## Discussion

Placebo means to please (from latin placere). It is proposed that placebo and opioid analgesics share a neuronal network [31]. The powerful placebo effect is summarized in a recent systematic review [32]. The vertebroplasty trials [33, 34] and the knee arthroscopy trial have demonstrated the effectiveness of sham surgery [35]. One early trial in patients with subacromial shoulder pain reported that sham ESWT was superior to ESWT [36].

Radial ESWT is being increasingly used for musculoskeletal complaints including subacromial shoulder pain, with and without calcification. Current evidence suggests that rESWT may have an effect on calcific tendinopathy of the shoulder, but there is no evidence so far to support the use of rESWT in subacromial shoulder pain without calcification [13, 14, 17, 27]. Most therapists use rESWT on shoulder pain without the use of imaging, and thus do not know whether they are treating a calcific shoulder or not. In this present study we treat patients with subacromial shoulder pain (with and without calcification) with supervised exercises and rESWT. We perform ultrasound examination before treatment and may therefore do subgroup analysis to evaluate if the results are different in the patients with calcific tendinopathy compared to the patients with non-calcific tendinopathy.

In the present study we have included sham treatment to make sure that any difference in results between the groups is due to the rESWT treatment, and not the placebo effect. All the patients get supervised exercises in addition to rESWT or sham, because this is the way most therapists use rESWT today. Exercise therapy is an evidence based treatment option for subacomial sholder pain, both in short- and long term [11, 37].

Because of the abundant use of rESWT, the results of this study will be of major interest. A positive result will support current practice, while no difference between the groups indicates that the use of rESWT for subacromial shoulder pain should not be recommended.

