## Sample size

A previous study indicates an expected standard deviation (SD) of 20 points [17]. To detect a difference in SPADI on 10 points between the groups with a statistical power of 80 % and a significance level of 0.05 we need 50 persons in each group. We have planned to include 144 persons to account for drop out and possibly higher variance.

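### The Discussion reads a null result as grounds not to recommend rESWT, but in this superiority trial a non-significant result can still be compatible with the 10-point benefit it was sized to detect

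*Protocol article*

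**What the plan says.** The last paragraph of the Discussion names two outcomes. A positive result would back the present use of rESWT, whereas "no difference between the groups indicates that the use of rESWT for subacromial shoulder pain should not be recommended". No third, inconclusive outcome is mentioned.

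The Sample size section sets out a superiority calculation: "To detect a difference in SPADI on 10 points between the groups" "with a statistical power of 80 % and a significance level of 0.05", with the SD taken from earlier work ("A previous study indicates an expected standard deviation (SD) of 20 points"). It arrives at 50 per group and then enlarges the trial: "We have planned to include 144 persons to account for drop out and possibly higher variance".

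The Statistical analysis section compares the change in SPADI from baseline to 24 weeks between the groups. Neither it nor the Discussion names a difference that must be excluded before the negative conclusion is drawn. The section on randomisation and blinding says that the interpretation will be written in two versions before the code is broken, but does not say how a null result is to be read.

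**The concern.** In a superiority trial with no margin, a finding of no difference will in practice mean that the test did not reject. That outcome covers two different situations. In one, the data rule out a benefit of the size the trial looked for. In the other, the data are compatible both with no benefit and with that full benefit. The Discussion sentence draws the same conclusion from both.

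This is an inference that the article states, not a detail it leaves out. Taken as written, it could turn an inconclusive result into advice against a widely used treatment, in a trial whose abstract expects to influence practice.

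**Working it through.** **Inputs** (all from the Sample size section unless noted): difference 10 points, SD 20, power 80 %, significance level 0.05 with sidedness not stated, 50 per group needed, 144 planned. Allocation is 1:1 (abstract), so 72 per group. No dropout rate is given, so I show a range from 72 analysed per group (no loss) to 50 (1 − 100/144 = 31 % loss).

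**The plan's own figure.** n per group = 2(z₁ + z₂)²·SD²/d², with z₁ for the significance level, z₂ for the power and d the difference.
- One-sided 0.05: 2 × (1.645 + 0.842)² × 400/100 = 49.5, so 50. This reproduces the stated figure.
- Two-sided 0.05: 2 × (1.960 + 0.842)² × 4 = 62.8, so 63.

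The sidedness question is a separate matter and nothing below depends on it. The intervals are two-sided 95 %.

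**Half-width of the interval.** h = t(0.975; 2n − 2) × SD × √(2/n).
- n = 72: standard error 20 × √(2/72) = 3.33; h = 6.59.
- n = 50: standard error 20 × √(2/50) = 4.00; h = 7.94.

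**Estimates that are non-significant and still compatible with 10.** An estimate e in favour of rESWT is non-significant if e < h, and its upper limit reaches 10 if e + h ≥ 10. Both hold for e between 10 − h and h.
- n = 72: 3.41 to 6.59.
- n = 50: 2.06 to 7.94.

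Examples at 72 per group: an estimate of 5 gives an interval from −1.6 to 11.6, which contains both 0 and 10. An estimate of 3 gives −3.6 to 9.6, which excludes 10; there the negative reading is justified against the 10-point target.

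**Sensitivity to the SD (assumed values).**
- SD 18, as covariate adjustment might achieve, n = 72: h = 5.93, range 4.1 to 5.9.
- SD 25, since the article allows for higher variance: h = 8.24 and range 1.8 to 8.2 at n = 72; h = 9.92 and range 0.1 to 9.9 at n = 50.

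**When the range would vanish.** It closes when 2h < 10. With the normal quantile and SD 20 this needs n > 2 × (2 × 1.96 × 20/10)² = 122.9, so 123 analysed per group, well above 72.

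**The case against.** The strongest reply is that the sentence carries less weight than this. It closes a paragraph on why the trial is of interest; it does not mention p-values, and no section of the article makes it an analysis rule. Declining to recommend an add-on that has failed to beat sham can also be a burden-of-proof position, which needs no proof of equivalence. And a superiority trial does not ordinarily need an equivalence margin; a reading based on the interval may well stand in the full protocol or the SAP.

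Much of this stands. Three stronger readings are tempting, and the article does not support them:
- A reader might take the sentence for a formal decision rule, or infer that it will govern the two blinded interpretations. It is an interpretive remark, and the section on randomisation and blinding neither cites it nor prescribes a reading of a null result.
- A reader might combine the 50-per-group figure with a two-sided test and conclude that the trial is underpowered, so that false negatives are unusually likely. The plan is 144. At 72 per group with SD 20, a true 10-point benefit would be missed in 14.9 % of two-sided tests; at 63 per group (12.5 % loss) in 19.9 %. Both are within the 20 % that the protocol accepts. The 29.5 % at 50 per group requires about 31 % loss, which the article does not predict.
- A reader might measure the harm by the chance of an inconclusive result when the true benefit is well below 10. Measured against a 10-point threshold, concluding that there is no worthwhile benefit would not then be an error.

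What survives is the inference itself. That a benefit was not shown differs from saying that the treatment should not be recommended. The article asserts the second without a condition.

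**Conclusion.** The point holds as a flaw in a stated interpretation, not in the design, the sample size or the analysis. With SD 20 and a two-sided 95 % interval, non-significant estimates favouring rESWT of about 3.4 to 6.6 points at 72 analysed per group, or 2.1 to 7.9 at 50, leave the 10-point benefit open. Smaller estimates exclude it.

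The result rests on the stated SD, on a simple comparison of two means and on 10 points as the reference. The article gives 10 only as the difference to detect and does not call it the smallest important difference. A lower SD narrows the range of affected estimates and a higher one widens it; at SD 18 and 72 per group it is still present. The sentence merits correction, but it does not threaten the trial's validity.

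**What to change.** Reword the last sentence of the Discussion so that the negative conclusion depends on the 95 % confidence interval for the 24-week between-group difference in SPADI change:
- Conclude that rESWT adds no worthwhile benefit only if the interval excludes the 10-point benefit used for sizing, or another worthwhile difference fixed before the analysis.
- If the interval contains both 0 and that value, report the result as inconclusive.

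Use the same reading in both versions of the blinded interpretation, with the direction of benefit set by the allocation that each version assumes.

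The cost is wording only; design, sample size and analysis stay as they are. The downside is that some null results must be called inconclusive, which is a less definite message than the article now promises.
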